## Abstract

**Background:**

High-flow nasal cannula oxygen therapy (HFNC) is recommended by some scholars as an optimized respiratory support method for blunt chest trauma (BCT) patients. The basis of this recommendation is limited, however, and the efficacy of HFNC or noninvasive ventilation (NIV) in BCT patients has not yet been rigorously explored. This study aims to determine if HFNC is non-inferior to NIV in reducing treatment failure in moderate to severe BCT patients with acute respiratory failure.

**Methods:**

This will be a prospective, open-label, multicenter, non-inferiority, randomized controlled trial. Moderate to severe BCT patients with acute respiratory failure (100mmHg < PaO_2_/FiO_2_ ≦ 200mmHg) who do not need immediate intubation will be randomized to HFNC or NIV within 48 h after trauma. The primary outcome is treatment failure, defined as invasive ventilation or a switch in respiratory support modality (from HFNC to NIV or vice-versa). Secondary outcomes include arterial blood gas analysis and vital signs at 2 and 12 h after initiating HFNC or NIV treatment, as well as patients’ comfort scores, dyspnea scores, daily number of nursing airway care interventions, incidence of pneumonia or pneumothorax, facial skin breakdown, duration of NIV or HFNC, 28-day mortality, and total ICU and hospital lengths of stay. Based on an *α* error of 5% and a *β* error of 80%, with a non-inferiority limit of 9%, a sample size of 562 will be required to accomplish the trial goal, considering potential patient dropouts and nonparametric analysis.

**Discussion:**

We hypothesize that HFNC will be non-inferior to NIV in reducing treatment failure in moderate to severe BCT with acute respiratory failure. The results should be useful for judging whether HFNC could be an effective alternative to NIV to treat moderate to severe BCT patients, especially for those who do not tolerate or have contraindications for NIV.

**Trial registration:**

Chinese Clinical Trial Registry ChiCTR1800017313. Registered on July 24, 2018.

**Supplementary Information:**

The online version contains supplementary material available at 10.1186/s13063-022-06507-2.

## Background

Blunt chest trauma (BCT) is a common traumatic injury, especially common in motor vehicle collisions or falls. Mortality due to BCT can be as high as 36% and is the second-leading cause of death in trauma after head injuries [1]. Acute respiratory failure is an important cause of death in patients with BCT. Fifty to 70% of chest trauma is accompanied by acute respiratory failure, and up to 20% develop acute respiratory distress syndrome [2, 3].

Invasive mechanical ventilation is recommended for severe BCT patients with decreased levels of consciousness, significant respiratory distress, airway obstruction, severe hypoxemia, or hemorrhagic shock. However, for moderate to severe BCT patients not accompanied by the above-mentioned conditions, invasive ventilation may increase the incidence of hospital-acquired pneumonia and prolong the duration of mechanical ventilation and intensive care unit (ICU) length of stay, all of which can lead to worse outcomes [4].

In recent years, several studies have found that noninvasive ventilation (NIV) had a beneficial effect on BCT patients with acute respiratory failure. Two randomized controlled studies found that for flail chest or multiple rib fractures with respiratory failure, NIV reduced mortality and the incidence of pneumonia by 28% and 34%, respectively, compared with invasive mechanical ventilation [5, 6]. In a randomized controlled trial comparing NIV to standard oxygen therapy in patients with a ratio of PaO_2_ to the fraction of inspired oxygen (FiO_2_) [PaO_2_/FiO_2_] less than 200 mmHg within 48 h after BCT, early continuous use of NIV significantly reduced the rate of intubation compared to standard oxygen therapy alone (12% vs 40%) and shortened their hospital stay by as much as 7 days [7].

A meta-analysis also showed that for BCT patients with intact neurological function, stable hemodynamics, and no obvious respiratory distress, early NIV could significantly reduce the rate of endotracheal intubation and complications, as well as shorten the hospital length of stay, with a NIV failure rate of only 12–18% [8]. However, patients with BCT often have facial injuries, which is a contraindication to NIV. In addition, about 15% of patients cannot tolerate NIV [9]. NIV intolerance may lead to increased rates of treatment failure and affect the overall clinical outcome.

Recently, Kourouche proposed a concept of the “ChIP” bundle treatment protocol for BCT, which involved respiratory support, analgesic medications, preventative therapies, and surgical treatments [10]. In this protocol, high-flow nasal cannula oxygen therapy (HFNC) is used, which is an emerging type of respiratory support system which can provide high-flow mixed gases through special nasal cannulas with higher temperature and humidity than standard nasal cannulas. HFNC is the preferred method of respiratory support in the ChIP bundle. It was reported that the application of the ChIP protocol reduced the incidence of pneumonia in patients with BCT by 56% [11]. However, no research to date has confirmed the contribution of HFNC to this protocol.

Up to now, there have been only two small retrospective studies exploring the application of HFNC in BCT. One study showed that 18% of 105 patients with moderate to severe BCT [Abbreviated Injury Scale (AIS) chest score ≥ 3] received endotracheal intubation due to treatment failure with HFNC [12]. This rate is similar to the 12–18% NIV failure rate previously reported in the literature [8]. In another retrospective study, compared with standard oxygen therapy, HFNC significantly reduced both the intubation rate and the ICU length of stay in patients with moderate to severe BCT [13]. However, to the best of our knowledge, there are no published studies directly comparing the efficacy of HFNC to NIV in patients with BCT. The present protocol is conceived to test the hypothesis that HFNC is non-inferior to NIV in reducing treatment failure in moderate to severe BCT patients with acute respiratory failure.

## Methods

### Design and setting

This study is a prospective, open-label, multi-center, non-inferiority, randomized controlled trial. It will be carried out in the trauma ICUs of five tertiary university teaching hospitals in China: Northern Jiangsu People’s Hospital (Yangzhou), Peking Union Medical College Hospital (Beijing), The First Affiliated Hospital of University of Science and Technology of China (Hefei), Suqian People’s Hospital of Nanjing Drum-Tower Hospital Group (Suqian), and The Second Affiliated Hospital of Soochow University (Suzhou).

We designed the protocol according to the Standard Protocol Items: Recommendations for Interventional Trials (SPIRIT) statement. This study was prospectively registered at Chinese Clinical Trial Registry on July 24, 2018 (ChiCTR1800017313). Patients are expected to be enrolled during a 36-month period starting in January 2019. A web-based randomization schedule will be used with a block size of 10, and patients will be allocated according to a ratio of 1:1 to the NIV or HFNC groups. Attending physicians and study participants cannot be blinded to their grouping since the devices are clearly different. However, the investigators will be excluded from clinical decisions and will be blinded to the patient group allocations.

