**Fig. 1 Fig1:**
[figure not shown]
Study flow chart according to CONsolidated Standards of Reporting Trials. BCT, blunt chest trauma; AIS, Abbreviated Injury Scale; PO_2_, partial pressure of oxygen; FiO_2_, fraction of inspiration oxygen; ABG, arterial blood gas; ICU, intensive care unit; HFNC, high-flow nasal cannula oxygen therapy; NIV, noninvasive ventilation

Eligible patients will be recruited by investigators (attending physicians) in each study hospital center. After participant selection, physicians will guide patients or their next of kin through informed consent (or refusal), which includes a brief introduction of the study, interventions, and the contact information of the investigators. A research assistant in each study center is then notified about patients who are willing to participate in this trial. Two copies of the informed consent are kept, one with the participants and one with the research team. The consent form and information materials are available from the corresponding author on request.

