Furthermore, we will also record any episodes of endotracheal intubation, or switching of respiratory support modality, including the reason and time for these events. We will also document any diagnosed episodes of pneumothorax or pneumonia, as well as each patients’ length of stay in the ICU and hospital, and their 28-day mortality.

Any decision to intubate a patient will be made by the patient’s attending physician. Criteria for intubation in this trial are cardiac arrest or apparent hemodynamic instability, significant hypoxemia (SpO_2_ < 85% while under sufficient oxygen therapy), respiratory acidosis with a pH < 7.25 under optimal medical management, severe disturbances of consciousness (Glasgow score <11), obvious aspiration or significantly reduced capacity for airway protection, active use of accessory muscles with thoraco-abdominal paradoxical movements, severe dyspnea (respiratory rate > 40 per minute), or respiratory depression (respiratory frequency < 8 per minute) [7].

All data will be collected on paper case report forms (CRFs) from patients’ electronic medical records. The data manager will collect CRFs and enter data to a dedicated web-based electronic database in de-identified form. The electronic data will be backed up, and the backed-up electronic data will be kept secure by the sponsor. The sponsor will check the data again according to the CRFs to ensure data accuracy. Treatment allocation will be anonymously processed to allow the independent statistician in this trial to be blinded. Only the trial investigators will have access to the final dataset.

The sponsor and statisticians will have access to the preliminary data set to enable needed statistical work. Doctors authorized by the sponsor will have access for data entry and for reviewing data at their site. Participants will be allocated an individual trial identification number and the allocation information will be stored in a separate, secure database. All data will be kept confidential and will not be disclosed. Anonymized trial data will be shared with other researchers upon reasonable request to contribute to future international prospective meta-analyses.

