## Trial status

The trial is currently recruiting patients. The final study protocol (version 3.0) was set on August 28, 2018. The first participant was enrolled on January 13, 2019. Recruitment was originally expected to be completed by December 31, 2021. Due to the impact of COVID-19, the recruitment completion time was delayed and is currently expected to complete by June 30, 2022.

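### A single published block size of 10, with unblinded treating physicians as recruiters, lets some upcoming allocations be deduced, mainly if blocks run within centre, which the article does not state

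*Protocol article*

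**What the plan says.** All references are to the protocol article.

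- **Allocation (Design and setting).** "A web-based randomization schedule will be used with a block size of 10". The two arms receive equal numbers (1:1). One size is given. Nothing in the text says that it varies or is withheld from sites. The trial runs in five hospitals, and the text does not say whether blocks run within each hospital or along one common list.
- **Blinding (Design and setting).** "Attending physicians and study participants cannot be blinded to their grouping since the devices are clearly different". The same paragraph then says that "the investigators will be excluded from clinical decisions and will be blinded to the patient group allocations".
- **Recruitment (Study population, text after Fig. 1).** "Eligible patients will be recruited by investigators (attending physicians) in each study hospital center".
- **Intubation (Data collection and management).** "Any decision to intubate a patient will be made by the patient’s attending physician". Intubation is one component of the primary outcome.
- **Timing (Trial status).** "The trial is currently recruiting patients", with completion expected by June 30, 2022.

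**The concern.** In a permuted block of known size, the remaining allocations are fixed once either arm has used its five places. Physicians who see which device each earlier patient received, and who know the block size, can work out some of what comes next. Here the people who decide whom to approach are the people who see the devices.

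The risk is selection before randomization. Some eligibility criteria need judgement, such as poor sputum clearance or a need for immediate intubation. A physician who foresees the next arm could decline a borderline patient or approach a different one. Intention-to-treat analysis does not remove a bias that enters before randomization.

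The article's stated safeguard is that investigators are blinded and kept out of clinical decisions. That does not fit with recruiting investigators who are attending physicians, cannot be blinded, and decide on intubation.

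**Working it through.** The plan gives no predictability figure to reproduce. The block scheme does not enter the sample size, so 562 is used below only as a count of patients.

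**Inputs from the article:** block size 10, ratio 1:1 (five places per arm), five centres, target 562.
**Assumptions:** the observer tracks past allocations. In steps 1 and 2 the observer sees the whole block sequence and knows where blocks start, as a site could if blocks ran within centre.

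**1. Allocations known with certainty, fixed block of 10.** The last *k* allocations are all known when they all belong to one arm: P = 2 × C(10−k, 5) / C(10, 5), with C(10, 5) = 252.

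| k | Probability |
|---|---|
| 1 | 2 × 126 / 252 = 1.000 |
| 2 | 2 × 56 / 252 = 0.444 |
| 3 | 2 × 21 / 252 = 0.167 |
| 4 | 2 × 6 / 252 = 0.048 |
| 5 | 2 × 1 / 252 = 0.008 |

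The sum is 1.667 per block, or 16.7%. Over the whole trial this is 0.1667 × 562 ≈ 94 patients.

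**2. Best guess, fixed block of 10.** Always name the arm with more places left. Expected correct guesses per block = 5 + (2¹⁰/252 − 1)/2 = 5 + (4.063 − 1)/2 = 6.53, or 65.3%. Chance gives 50%. The excess is 0.153 × 562 ≈ 86 correct guesses. Smaller fixed blocks are worse: a block of 6 gives 25% certain and 68.3% guessed, and a block of 4 gives 33% and 70.8%.

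**3. One central unstratified list.** A site sees only its own patients and names the arm it has used less. Simulation (1,500 lists of 562) gives 51% correct for a site with 20% of recruitment and 53% for a site with 80%. Site shares are not in the article, hence the range.

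**4. Varied blocks.** The simulated observer sees the whole list, knows the set of sizes and that each is equally likely, does not know their order, and updates by Bayes' rule. Results are from 600 lists of 112 (about 562/5) and 200 lists of 562.

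| Scheme | Certain | Guessed correctly |
|---|---|---|
| Fixed 10 | about 16% (the last block may be incomplete) | about 65% |
| 8, 10, 12 | about 1% | about 65% |
| 4, 6, 8 | about 2% | about 68% |

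Varying the size does not lower the average guess rate. It takes away the certainty.

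**5. Illustration of the stake.** Suppose a recruiter always steers between patients whose failure risks differ by 5 to 10 points (assumed). Using only the certain allocations shifts the risk difference by 0.167 × 5 to 0.167 × 10, which is 0.8 to 1.7 points. Acting on every best guess shifts it by (0.653 − 0.347) × 5 to (0.653 − 0.347) × 10, which is 1.5 to 3.1 points. The margin is 9 points. These are upper-end cases with consistent steering, and the shift could favour either arm.

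**The case against.** The strongest reply is that the article describes one web-based schedule for five centres and mentions no stratification. If that is a single central list, step 3 shows that a site can infer almost nothing. A condensed article may leave this detail to the full protocol, so its absence is not itself a fault. This stands, and it limits the point: a reader might infer that upcoming allocations are generally predictable, and the text does not support that. Even in the worst case, five in six allocations are not certain, and a block of 10 leaks less than a block of 4 or 6.

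Other replies also carry weight:

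- Consent precedes randomization, the web system hides the next assignment, and the 48-hour and 3-hour windows limit how long a patient can be deferred. None of these prevents a patient from being declined.
- A reader might infer that the primary analysis wrongly lacks a centre term. The analysis plan is not shown and may contain one. In any case, stratifying the analysis by centre would not remove steering that happens within a centre.
- The investigators described as blinded may be a different group from the recruiters. If so, the article uses one word for two roles and should separate them.
- Recruitment was near its expected end, and the number of patients still to be randomized is not given.

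**Conclusion.** The weakness is real but conditional and modest. A fixed, published block size combined with unblinded recruiting physicians allows some allocations to be deduced. If blocks run within centre and recruiters keep count, 16.7% are certain and about 65% can be guessed. With one central list the guess rate is about 51% to 53%. The article does not say which applies. The figure of 94 patients is the worst case over the whole trial, not the number that a change could still protect. Nothing in the document shows that any steering has taken place.

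The contradiction about investigators does not depend on the list structure. As written, they cannot be both blinded and outside clinical decisions and also be the attending physicians who recruit and decide on intubation.

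**What to change.** 1. For all remaining allocations, use block sizes that vary at random, are not disclosed to sites, and average no less than 10, for example 8, 10 and 12. Do not move to smaller sets such as 4, 6 and 8.
2. State whether blocks run within centre or along one list. If the list is central, do not add centre stratification for this purpose alone: it would raise what a site can guess from about 51–53% to about 65%.
3. Reconcile the sentence on blinded investigators in Design and setting with the recruitment text after Fig. 1 and the intubation sentence in Data collection and management. Say which role recruits, which treats, and which is blinded.

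**Cost.** The web list has to be reconfigured and a few sentences clarified. The largest possible difference between arms at the end of a list rises from 5 (half of 10) to 6 (half of 12). The sample size is unaffected. The gain is limited to patients not yet randomized.

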### Study population

Adult patients with moderate to severe BCT (AIS chest score ≥ 3) admitted within 48 h after a traumatic injury will be eligible if moderate hypoxemia (100mmHg < PaO_2_/FiO_2_ ≦ 200mmHg) developed while receiving standard oxygen therapy (mask ≥6 L/min). AIS chest score will be performed according to the method described by Baker et al. [14].

Patients in one or more of the following criteria will be excluded (see Fig. 1): less than 18 years old, open chest trauma, those requiring immediate endotracheal intubation (for example, if a patient’s respiratory rate is > 40 times per minute or in respiratory arrest), severe injuries such as ruptured abdominal organs, decreased consciousness (severe brain injuries, Glasgow score <11), unstable hemodynamics (requiring dopamine > 8 μg/kg/min or norepinephrine > 0.2 μg/kg/min), need for urgent surgery, NIV contraindications (oral and facial trauma, poor sputum clearance capacity, tracheotomy, vomiting or aspiration), or nasal injuries affecting the insertion or stability of nasal prongs (such as nasal bone fractures or significant nasal epistaxis).

**Fig. 1 Fig1:**
[figure not shown]
Study flow chart according to CONsolidated Standards of Reporting Trials. BCT, blunt chest trauma; AIS, Abbreviated Injury Scale; PO_2_, partial pressure of oxygen; FiO_2_, fraction of inspiration oxygen; ABG, arterial blood gas; ICU, intensive care unit; HFNC, high-flow nasal cannula oxygen therapy; NIV, noninvasive ventilation

Eligible patients will be recruited by investigators (attending physicians) in each study hospital center. After participant selection, physicians will guide patients or their next of kin through informed consent (or refusal), which includes a brief introduction of the study, interventions, and the contact information of the investigators. A research assistant in each study center is then notified about patients who are willing to participate in this trial. Two copies of the informed consent are kept, one with the participants and one with the research team. The consent form and information materials are available from the corresponding author on request.

### Study groups

Within 3 h of meeting inclusion criteria and obtaining informed consent, patients will be randomly allocated to receive either NIV or HFNC. Patients randomized to the HFNC group will receive HFNC (AIRVO™ 2, Fisher & Paykel Healthcare, Auckland, New Zealand) using suitable large-bore nasal prongs selected according to the size of the patients’ nostrils. The initial airflow will be set at 50 L/min and adjusted according to patient tolerance. To reach an absolute humidity of 44mg H_2_O/L, the temperature will be set to 37°C. FiO_2_ will be initially set at 1.0 and adjusted to maintain a SpO_2_ ≥ 92%. HFNC will be continuous if it is well tolerated, or it can be used intermittently according to clinician decision. During the termination of HFNC, standard oxygen therapy will be used to maintain a SPO_2_ ≥ 92%.

Subjects randomized to the NIV group will receive NIV (BiPap Vision or PHILIPS V60) in spontaneous or timed (S/T) mode using a standard oral-nasal (full-face) mask (RT040). The parameters will be adjusted adaptively: the expiratory positive airway pressure (EPAP) settings will be increased gradually from 4 cmH_2_O to make sure the patient can trigger the ventilator with each inhalation. The inspiratory positive airway pressure (IPAP) will be initially set to 8 cmH_2_O and gradually increased to achieve a satisfactory tidal volume (8mL/kg) with acceptable tolerance. The pressure level and FiO_2_ will be adjusted to maintain a respiratory rate ≤ 28/min and a SpO_2_ ≥ 92%. The NIV should be applied as continuously as possible for 24 h. To improve tolerance, a short break from NIV will be allowed with the consent of the attending physician. Oxygen therapy during any interruption of NIV will be the same as for the HFNC group.

Patients in both groups will be in a semi-recumbent position unless contraindicated. A multi-modal pain control regimen will be adopted in all participants. Epidural analgesia with sufentanil plus bupivacaine will be preferred, combined with oral celecoxib (200 mg twice daily). When the visual analogue scale of pain is greater than 6, 100 mg tramadol will be given intravenously as a remedial treatment. For patients with contraindications to regional anesthesia (acute spine fracture, unstable pelvic fracture, coagulopathy, et al.), analgesia based on intravenous remifentanil will be administered, and the dosage will be determined using pain scales. In addition to respiratory support and pain management, other treatments will be supplied to both groups according to current guidelines, including hemostasis, external fixation of the chest wall, thoracentesis or thoracic closed drainage, fluid resuscitation, blood transfusion, or any surgical operation, if necessary [15].

